## Methods

### Study design

This is a multi-centre, randomised, wait-list controlled pilot study. This study will determine the effectiveness of GBH by comparing two groups: the immediate GBH treatment group and the waiting treatment group. Furthermore, the findings before and after GBH treatment will be compared in each group. The immediate treatment group will undergo an 8-week treatment period and an 8-week follow-up period. The waiting treatment group will undergo an 8-week waiting period and an 8-week treatment period. An overview of the trial process is shown in Fig. 1.

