### Intervention

The immediate treatment group will receive GBH for 8 weeks on enrolment, and the waiting treatment group will receive GBH for 8–16 weeks at 8 weeks after enrolment. Every participant will receive 3.0 g of GBH (Hanpoong Pharm & Food Co., Ltd) twice a day for 8 weeks. GBH is a light-brown granular substance consisting of Cinnamomi Ramulus, *Wolfiporia extensa*, *Paeonia suffruticosa* Andrews, *Prunus persica*, and *Paeonia lactiflora* in an equal ratio. Any other medicine or treatment that may affect shoulder pain and hyperlipidaemia will be prohibited during the study period.

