### Data collection

The following demographic data will be collected on the enrolment date: age, sex, occupation, height, weight, alcohol habit, and smoking status. Blood tests and blood stasis questionnaire evaluation will be conducted and VAS scores for shoulder pain will be assessed during the screening visit. After randomisation, the ankle–brachial pressure index (ABI), brachial–ankle pulse wave velocity (baPWV), oxygen saturation (SpO_2_), total haemoglobin (SpHb), pleth variability index (PVI), oxygen content (SpOC), pulse rate (PR), methaemoglobin (SpMet), perfusion index (PI), blood pressure (BP), body mass index (BMI), and waist circumference (WC) will be assessed (visit 1). Blood tests, blood stasis questionnaire evaluation, and VAS score evaluation will be conducted again during visit 1 in the waiting treatment group since the subjects are required to wait for 8 weeks after randomisation. SpO_2_, SpHb, PVI, SpOC, PR, SpMet, and PI will be measured using an oximeter (Masimo Corp.). Blood tests, blood stasis questionnaire evaluation, and oximeter measurements will be performed and shoulder pain, ABI, baPWV, BP, BMI, and WC will be assessed every 4 weeks after GBH has been received (visits 2 and 3). Furthermore, compliance and adverse events will be assessed every 4 weeks (visit 2 and 3), and patient satisfaction will be evaluated after 8 weeks of intervention (visit 3). At the follow-up visit in the immediate treatment group, blood tests, blood stasis questionnaire evaluation, oximeter measurements, assessment of shoulder pain, and determination of ABI, baPWV, BP, BMI, and WC will be performed (visit 4). The time points of the evaluations are presented in Table 1.

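### In weeks 0–8 the immediate group's pain VAS is taken at weeks 0, 4 and 8 but the waiting group's only at 0 and 8, so week 4 has no randomised control and LOCF works unequally

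*Protocol article*

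**What the plan says.** The article's Study design section sets up the periods: "The immediate treatment group will undergo an 8-week treatment period and an 8-week follow-up period", and "The waiting treatment group will undergo an 8-week waiting period and an 8-week treatment period". It bases the effectiveness question on the contrast between the groups: "This study will determine the effectiveness of GBH by comparing two groups: the immediate GBH treatment group and the waiting treatment group". Changes before and after GBH within each group are planned as well.

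The Data collection section sets the timing of the primary outcome:

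- Both groups: "VAS scores for shoulder pain will be assessed during the screening visit".
- Waiting group: "VAS score evaluation will be conducted again during visit 1 in the waiting treatment group since the subjects are required to wait for 8 weeks".
- Both groups, once on treatment: shoulder pain "will be assessed every 4 weeks after GBH has been received (visits 2 and 3".
- A further assessment, visit 4, is described only "At the follow-up visit in the immediate treatment group".

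No assessment of the waiting group during the wait is described. The Statistical analyses section fills missing values by LOCF. The inclusion criteria require a VAS of at least 4 out of 10, and the trial is open-label.

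**The concern.** The clock for the 4-weekly VAS starts with GBH, not with randomisation, so the two groups are measured on different schedules in the one window where the randomised comparison of GBH with no GBH can be made. Two things follow.

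First, one of the immediate group's two on-treatment readings in that window has no counterpart in the waiting group. It can be read only as change within a group, which mixes any drug effect with natural course and regression to the mean. Regression to the mean is to be expected when entry requires a minimum pain score.

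Second, the schedule interacts with the missing-data rule. In one group LOCF can carry a value that already reflects four weeks of natural course plus treatment. In the other it can carry only the entry score. Part of the week-8 difference can then come from the visit calendar and not from GBH.

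**Working it through.** The plan states no figure for this point. The sample size of 40 comes without an effect size, standard deviation or power, and nothing below depends on one. The check is to rebuild the schedule and then follow LOCF through it.

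**Step 1. VAS times in weeks from randomisation.** Screening is taken as week 0, GBH as starting at week 0 (immediate) or week 8 (waiting), and visit 4 as falling at the end of the 8-week follow-up.

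| Assessment | Immediate | Waiting |
|---|---|---|
| Screening | 0 | 0 |
| Visit 1 (VAS repeated in waiting group only) | – | 8 |
| Visit 2 (GBH start + 4) | 4 | 8 + 4 = 12 |
| Visit 3 (GBH start + 8) | 8 | 8 + 8 = 16 |
| Visit 4 | 8 + 8 = 16 | – |

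The times common to both groups are 0, 8 and 16. By week 16 both groups have had GBH, so week 8 (immediate visit 3 against waiting visit 1) is the only post-baseline time at which treated and still-untreated randomised groups are both measured. Week 4 exists in the immediate group alone.

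**Step 2. Which value LOCF carries to week 8.**

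| Participant leaves | Immediate carries | Waiting carries |
|---|---|---|
| Before week 4 | screening | screening |
| Between weeks 4 and 8 | week 4, on treatment | screening |

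Only the second row is unequal. For scale, 40 participants at 1:1 give 20 per group, and 25% drop-out gives 0.25 × 20 = 5 per group. If all of it fell in weeks 0–8 (an assumption; the article does not say over which period the 25% applies), all 5 waiting drop-outs would carry the screening VAS. In the immediate group, 0 to 5 would carry a week-4 value, depending on when they left.

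**Step 3. Size.** Let q be the share of each group leaving between weeks 4 and 8, n4 and n8 the improvement without any drug effect by weeks 4 and 8, and d4 and d8 the extra improvement from GBH. Assume that those who leave have the same averages as those who stay.

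- Immediate mean improvement under LOCF: (1 − q)(n8 + d8) + q(n4 + d4)
- Waiting mean improvement under LOCF: (1 − q)n8 + q × 0
- Difference: (1 − q)d8 + q(d4 + n4)
- Error against the true d8: q(d4 + n4 − d8)

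If GBH has no effect (d4 = d8 = 0), the error is q × n4. With n4 = 1 point (assumed):

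| q | Drop-outs per 20 | Spurious difference favouring GBH |
|---|---|---|
| 0 | 0 | 0 |
| 0.125 | 2.5 | 0.125 |
| 0.25 | 5 | 0.25 |

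The figure scales with n4 and changes sign if untreated pain worsens. Adjusting for baseline does not remove it, because the carried screening value is itself the baseline.

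**Step 4. With a week-4 VAS in the waiting group.** The waiting mean becomes (1 − q)n8 + q × n4, and the difference becomes (1 − q)d8 + q × d4. The n4 term cancels. What remains, q(d4 − d8), is the usual LOCF shortfall when the effect is still growing. Participants who leave before week 4 carry the screening value in both groups, as before.

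**The case against.** The strongest reply is that no stated analysis is broken. The week-8 contrast is complete in both groups, and the article promises no between-group test at week 4. The 4-week on-treatment VAS also has a use: it exists in both groups (weeks 4 and 12) for the planned before-and-after comparisons. The Discussion already concedes the open-label wait-list design, possible bias in a self-reported VAS, and a wish to limit participant burden. Less contact during the wait is largely inherent in such a control. All of this stands, and it keeps the point small. It does not answer the unequal LOCF, and the limitations listed in the Discussion do not include the gap in the middle of the wait.

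Three stronger readings are tempting, and the document does not support them:

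- A reader might infer that the randomised comparison is invalid. It is not; week 8 is intact.
- A reader might infer that a week-4 reading would make the main result clearly more precise. A gain of that kind belongs to an analysis of the mean of weeks 4 and 8. That is a different quantity from the week-8 effect, and it can lose power if the effect builds slowly. With complete data, little of the gain reaches a week-8 analysis.
- A reader might infer that other treatment in the waiting group goes unchecked and dilutes the contrast. The Intervention section does say "Any other medicine or treatment that may affect shoulder pain and hyperlipidaemia will be prohibited during the study period", and the text describes no contact during the wait. But how such use is recorded is detail that a condensed article may leave to the full protocol, and any size put on the dilution would rest on assumed figures alone.

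The schedule table is not reproduced in the text at hand and could not be checked. Its legend does not point to a visit during the wait.

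**Conclusion.** The point holds as a low-cost improvement, not as a fault that undermines the trial. The difference in schedules follows directly from the text. The week-4 reading of the primary outcome is lost to the randomised comparison, and LOCF treats the two groups differently for anyone who leaves between weeks 4 and 8.

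The size of the second effect is illustrative: 0 to 0.25 VAS points for each point of improvement by week 4 that is not due to the drug. The upper end needs the entire 25% drop-out to fall between weeks 4 and 8 in both groups, which is an extreme case. If GBH works and its effect grows after week 4, the two errors partly offset each other, and the net error favours GBH only when n4 exceeds d8 − d4.

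**What to change.** Schedule the VAS by weeks from randomisation in both groups by adding a week-4 VAS in the waiting group. Use one self-completed form in both groups, for example a take-home or mailed paper VAS, with the same question on other shoulder treatment used since randomisation. A telephone score in one group set against a clinic score in the other would add a difference of mode to an unblinded primary outcome, so that should be avoided.

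Keep week 8 from randomisation as the main between-group time point and report week 4 as a secondary randomised comparison. For participants already past week 4 when the change takes effect, say that no value exists.

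The cost is one short contact for about 20 participants, slightly more attention in the waiting group, one schedule line and a protocol amendment. No extra clinic visit or blood test is needed. Trial status reports recruitment from June 2019 with five enrolled as of July 2019, so on those figures an amendment made then would have missed few participants. The same schedule should carry over to the full-scale trial. If no amendment is made, the plan should at least state that week 8 is the only between-group time point and that week 4 is descriptive.

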**Table 1 Tab1:**
[figure not shown]
Study schedule of the GBH pilot study

*ABI* ankle–brachial pressure index, *BaPWV* brachial–ankle pulse wave velocity, *BMI* body mass index, *GBH* Gyejibongnyeong-Hwan, *WC* waist circumference

^*^ Applies only to immediate treatment group

✔ applies only to wait-list treatment group

### Outcome measures

#### Primary outcome

The primary outcome is shoulder pain. This will be assessed using VAS scores, which are the patient-reported outcome. Lower VAS scores will indicate that GBH successfully reduced shoulder pain.

#### Secondary outcomes

The secondary outcomes include the blood stasis score, the high-density lipoprotein cholesterol (HDL-C), low-density lipoprotein cholesterol (LDL-C), TG, TC, fasting blood glucose (FBG), resistin, C-reactive protein (CRP), serum amyloid P (SAP), and D-dimer levels, ABI, baPWV, BP, BMI, WC, and the seven oximetry indices (SpO_2_, SpHb, PVI, SpOC, PR, SpMet, and PI). Blood stasis scores, ABI, baPWV, oximetry indexes, and levels of resistin, CRP, SAP, and D-dimer will be used to evaluate blood stasis. CRP, as an inflammation marker, will be also used as an outcome of trapezius myalgia treatment [16]. HDL-C, LDL-C, TG, TC, and FBG levels, BP, BMI, and WC will be measured to verify the effectiveness of GBH for treating metabolic diseases referred to in previous studies.

### Statistical analyses

All analyses will be conducted according to the intention-to-treat (ITT) principles. All statistical analyses will be two-sided, and statistical significance will be set at 0.05. The last-observation-carried-forward (LOCF) method will be used to input missing values. An independent *t* test or Wilcoxon rank-sum test will be used to compare changes in scores after performing the Kolmogorov–Smirnov test to confirm the normality of the distribution. All values will be presented as mean and standard deviation values or *n* (%) unless stated otherwise. Outcome variables will be analysed using the corresponding analysis of covariance (ANCOVA) considering the baseline scores as covariates. All statistical analyses will be performed using the SAS statistical package, version 9.4 (SAS Inc., Cary, NC, USA).

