## Background

Shoulder pain is a feeling of stiffness or discomfort around the shoulder joint, especially in the trapezius muscle. The incidence of shoulder pain in primary care is 14.7 per 1000 patients per year, and approximately 70% of the population experiences more than one episode in a lifetime [1–3]. Electrotherapy (transcutaneous electrical nerve stimulation, TENS), ultraviolet therapy, hot pack, massage, and sodium channel blocker drugs are used to alleviate muscle contractions; however, these interventions are largely ineffective [4, 5]. The tension in the shoulder muscles worsens with prolonged sitting at a computer and improper posture, and under physical and emotional stress. Myalgia is caused by the accumulation of lactic acid in the muscles and impaired blood circulation. In traditional East Asian medicine, muscle cramps and chronic musculoskeletal pain are considered to be due to blood stasis and can lead to limitations in shoulder movements by blocking the meridians [6].

Blood stasis is defined as the pathological stagnation of blood in certain parts of the body. It manifests as a variety of symptoms, including pain in a fixed location, a dark-purple appearance of the face or tongue, bleeding, blood spots under the skin, and an astringent pulse [7]. It is believed that blood stasis causes lipoprotein disorders such as thrombosis and the formation of atheromatous plaques [8–10]. Several herbal formulae that reduce blood stasis are helpful in the management of metabolic disorders [11]. Furthermore, blood stasis can occur after physical injuries, and the use of herbal medicine to eliminate blood stasis has been reported to alleviate muscle pain in some cases [12].

Therefore, we hypothesised that Gyejibongnyeong-Hwan (GBH), a herbal formula for dissipating blood stasis, is effective for the treatment of shoulder pain and hyperlipidaemia. GBH was approved as a medicine for shoulder discomfort by the Ministry of Food and Drug Safety (MFDS), South Korea [13]. In previous studies, GBH has been reported to ameliorate metabolic diseases such as hyperglycaemia and hyperlipidaemia [14, 15]. The primary objective of this pilot trial is to explore whether GBH relieves shoulder pain related to blood stasis. The secondary objective is to determine whether GBH is also helpful in improving blood lipid levels associated with blood stasis.

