### Sample size

This trial is a pilot study that examines the feasibility of conducting a large-scale randomised clinical trial for the use of GBH to treat shoulder pain related to blood stasis. No adequate references could be found with regard to the sample size; hence, a sample size of 40 patients is determined to be adequate considering a 25% drop-out rate. Participants will be assigned to either the immediate treatment group or the waiting treatment group at a ratio of 1:1.

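### Two unranked analyses of the primary VAS comparison, a normality-gated change-score test and a baseline-adjusted ANCOVA, are both set at 0.05; name the ANCOVA as the one that decides

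*Protocol article*

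**What the plan says.** The Statistical analyses section gives one significance rule for everything: "All statistical analyses will be two-sided, and statistical significance will be set at 0.05". It then describes two ways of comparing the groups.

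- **Change-score test.** An independent t test or a Wilcoxon rank-sum test "will be used to compare changes in scores after performing the Kolmogorov–Smirnov test to confirm the normality of the distribution".
- **ANCOVA.** "Outcome variables will be analysed using the corresponding analysis of covariance (ANCOVA) considering the baseline scores as covariates".

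Neither is called primary, supportive or sensitivity. The Primary outcome section names shoulder pain and says only how it is measured: "This will be assessed using VAS scores, which are the patient-reported outcome". It attaches no analysis to that outcome, and no other section ranks the two methods.

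The aim is exploratory: "The primary objective of this pilot trial is to explore whether GBH relieves shoulder pain related to blood stasis". The sample size has no effect size, SD or power behind it. The Sample size section says "No adequate references could be found with regard to the sample size", and that "a sample size of 40 patients is determined to be adequate considering a 25% drop-out rate".

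**The concern.** VAS is a continuous score, so both analyses apply to it and each yields its own p-value at 0.05. When they disagree, the plan does not say which is the trial's result.

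Two things are at stake. First, if a significant result from either may be reported as the finding, the chance of a false positive is above the stated 5%. Second, if the change-score test becomes the headline, the trial gives up precision that the recorded baseline would supply at no cost. Inside the change-score branch, a pre-test on the data also decides whether the reported quantity is a mean difference (t) or a rank comparison (Wilcoxon).

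The abstract says that the pilot will form the basis of a full-scale trial, and the Discussion ties further trials to its results. An unclear headline estimate serves that purpose poorly. The trial is also open-label, which makes it more useful to settle the deciding analysis before the data are examined.

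**Working it through.** **Inputs from the article.** Two-sided 0.05 (Statistical analyses); 40 patients, 1:1, 25% drop-out (Sample size); entry requires VAS of at least 4 (Inclusion and exclusion criteria).

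**Inputs assumed, because the article gives none.** Baseline-to-follow-up correlation r from 0.2 to 0.8; equal SDs at the two times; SD 2 and an untruncated mean VAS of 4 to 5 where truncation is modelled; a true effect of 0.8 SD where power is shown.

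**The plan's own figures.** The 0.05 is a set level, with nothing to reproduce. For the sample size, 30 / (1 − 0.25) = 40, so 40 is consistent with 30 completers (15 per arm), but there is no power calculation to check.

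**Step 1: error rate if either result may be claimed.** Two independent tests would give 1 − 0.95² = 0.0975. These two share data and are correlated, so the true figure is lower. Simulation with 40,000 trials per setting, normal data, untruncated baseline, and a Kolmogorov–Smirnov gate at 5%:

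| r | Either significant, 20 per arm | Either significant, 15 per arm |
|---|---|---|
| 0.2 | 0.080 | 0.081 |
| 0.5 | 0.072 | 0.075 |
| 0.8 | 0.064 | 0.065 |

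Taken alone, the gated test held 0.050–0.052 and ANCOVA 0.048–0.052. With baseline truncated at VAS 4 (mean 5, SD 2, r = 0.5), the either-significant rate was 0.068 at both sizes. Two further simulations with truncation, for r from 0.3 to 0.7, gave 6.0–7.0% and 6.6–7.4%. Together this is about 6–8%.

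**Step 2: precision.** With equal SDs, in units of SD², the ANCOVA residual variance is 1 − r² and the change score's variance is (1 − r²) + (1 − r)²V, where V is the baseline variance after selection. The ratio ANCOVA/change is (1 − r²) / [(1 − r²) + (1 − r)²V].

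- No truncation, V = 1: 0.65, 0.75 and 0.85 at r = 0.3, 0.5 and 0.7.
- Truncated at 4, mean 4, SD 2: V = 1 − 2/π = 0.363. At r = 0.3 the ratio is 0.91 / (0.91 + 0.49 × 0.363) = 0.836; at 0.5 and 0.7 it is 0.892 and 0.940.
- Truncated at 4, mean 5, SD 2: the cut is at z = −0.5, λ = φ(0.5)/Φ(0.5) = 0.509, V = 1 − 0.5 × 0.509 − 0.509² = 0.486. The ratios are 0.793, 0.861 and 0.921.

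Estimating the slope costs ANCOVA a factor of about 1 + 1/(40 − 4) = 1.028 with 40 analysed. The truncated ratios then become:

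| r | Mean 4 | Mean 5 | ANCOVA variance lower by |
|---|---|---|---|
| 0.3 | 0.860 | 0.815 | 14–19% |
| 0.5 | 0.917 | 0.884 | 8–12% |
| 0.7 | 0.966 | 0.947 | 3–5% |

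**Step 3: power and disagreement.** With truncation (mean 5, SD 2), r = 0.5 and an effect of 0.8 SD (1.6 points), power for the gated test against ANCOVA is 0.75 v 0.80 at 20 per arm and 0.62 v 0.67 at 15. The two verdicts differ in 10% and 12% of trials. A separate truncated simulation with a 1.5-point effect and r from 0.3 to 0.7 gave disagreement in 5–16% of trials.

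**The case against.** The strongest reply is that this is a pilot with an exploratory objective and no power calculation, so no confirmatory claim rests on the 5% level. The article never says that either result may be claimed, it condenses a fuller protocol, and ranking a main model against supporting ones is often left to an analysis plan. Baseline-adjusted ANCOVA is already in the text; only its priority is missing. This stands as a limit on severity. It does not remove the point, because the article itself fixes two complete analyses of the same outcomes at the same level, one of them less precise and chosen by a pre-test.

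A reader might infer more than the article supports:

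- **That the error rate is above 5% as planned.** It is so only under an either-result rule, which the article does not state.
- **That the normality gate itself inflates error.** Under normal data the gated test stayed at or below 0.052. The pre-test has limited ability to detect skewness at this size, but that is not a demonstrated error in the VAS result.
- **That selecting on VAS of at least 4 makes change scores especially inefficient.** The reverse holds. Selection shrinks baseline variance, so the ratio moves closer to 1 (0.84–0.94 for mean 4 in large samples, against 0.65–0.85 untruncated).
- **That t and ANCOVA aim at different effects.** Under randomisation both estimate the same mean difference. Only Wilcoxon targets something else.
- **That t and Wilcoxon count as two looks.** The plan picks one of them through the gate.

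**Conclusion.** The point holds as a defect in what is written: two unranked verdicts on one primary outcome. The inflation is about 6–8% instead of 5%, conditional on either result being claimable and on an assumed correlation of 0.8 down to 0.2. The precision loss from letting the change-score test decide is roughly 3–19% of variance for r from 0.7 down to 0.3, under assumed SD 2, baseline truncated at VAS 4 and 40 analysed; at high correlation it is minor. SD, correlation and effect are not in the article, so these are ranges and not estimates for this trial. The consequence is an ambiguous headline result for planning the full-scale trial, not a failed confirmatory error rate. It is worth correcting because the better method is already in the text and uses data already collected.

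**What to change.** In Statistical analyses, name a single primary analysis: ANCOVA of week-8 VAS on treatment group with screening VAS as covariate, reported as an adjusted mean difference with 95% CI. By the Data collection section, week 8 is visit 3 in the immediate group and visit 1, after the wait, in the waiting group. Screening VAS is the baseline taken before randomisation in both groups.

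Remove the Kolmogorov–Smirnov gate, and label any t or rank-based comparison of change scores as a sensitivity analysis that does not alter the primary conclusion.

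Adjustment for site, a permutation version of the ANCOVA and log-transformation of skewed biomarkers are optional and not needed to resolve this point. The cost is a change of wording: no new data, visits or patients.
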